## Abstract

**Background:**

Treatment of disorders of consciousness (DOC) remains a clinical challenge. Electroacupuncture (EA) was shown to have the potential to promote the recovery of consciousness. This trial aims to explore the therapeutic effects and mechanisms of EA in patients with DOC due to traumatic brain injury (TBI) through a multimodal approach.

**Methods:**

A total of 50 adult patients with DOC due to TBI and 25 healthy subjects will be enrolled in the study. Patients enrolled in the study will be assigned to the EA group or the sham‐EA group through stratified randomization. All patients receive behavioral assessments (CRS‐R and brain–computer interface), neurophysiological evaluations (EEG, somatosensory evoked potentials, brainstem auditory evoked potentials), and neuroimaging evaluations (rs‐fMRI, amide proton transfer, intravoxel incoherent motion, neurite orientation dispersion and density imaging) before and after the 14‐day EA or sham‐EA treatment. Each healthy subject will receive a set of neurophysiological and neuroimaging examinations but no treatments. The practitioner administering EA and sham‐EA is the only one aware of the grouping results. In the sham‐EA group, sham‐acupoints, sham‐acupuncture, and sham‐wire are utilized. The primary outcome measurement is the change in CRS‐R score after 14 days of treatment compared with the baseline CRS‐R score.

**Discussion:**

The AcuDoc trial will be the first randomized sham‐controlled study to investigate the clinical benefits of EA in patients with DOC. This trial will elucidate the role of EA in the treatment of DOC due to TBI and provide evidence of its therapeutic mechanisms.

## Background

1

With the rapid development of life support technology, an increasing number of patients can survive severe brain injury. Some survivors regain consciousness after a period of coma; however, many patients develop prolonged disorders of consciousness (DOC), which poses a therapeutic challenge for clinicians and a heavy burden for their families (Thibaut et al. 2019).

In recent years, many new therapeutic interventions have been attempted to improve the recovery of consciousness: pharmacological treatments include dopamine agonists and N‐methyl D‐aspartate antagonists (amantadine), gamma‐aminobutyric acid agonists (baclofen, zolpidem, and midazolam), and calcium channel blocker (ziconotide); non‐pharmacological treatments include transcranial direct current stimulation (targeting the cortex), repeated transcranial magnetic stimulation (targeting the cortex), low‐intensity focused ultrasound pulse (targeting the central thalamus), deep brain stimulation (targeting the central thalamus), vagal nerve stimulation (targeting the brainstem), spinal cord stimulation (targeting the brainstem), and sensory stimulations (targeting various sensory pathways) (Thibaut et al. 2019). However, only two trials have shown class II evidence (Giacino et al. 2012; Thibaut et al. 2014), and interventions stimulating other neural pathways and circuits also need to be explored.

According to traditional Chinese medicine theory, acupuncture at Shuigou point (also known as Renzhong, GV 26, DU 26) can “wake up the brain and open orifices” and has been used to improve the recovery of consciousness for more than a thousand years (Li and Liang 2016). In recent years, many studies have investigated the therapeutic effects and mechanisms of acupuncture at Shuigou in restoring consciousness. A meta‐analysis of 14 randomized controlled trials, with sample sizes ranging from 29 to 150, demonstrated that EA significantly improved the Glasgow Coma Scale and Glasgow Outcome Scale scores in traumatic brain injury (TBI) patients with coma, and Shuigou was the most commonly used acupoint in these trials (Chen et al. 2021). A self‐controlled functional near‐infrared spectroscopy study involving 16 DOC patients demonstrated that acupuncture at Shuigou increased the concentration of oxygenated hemoglobin in the prefrontal cortex and strengthened the connection strength of the left cerebral cortex (Xin et al. 2022). A self‐controlled motor‐evoked potential test study involving 14 DOC patients indicated that acupuncture at Shuigou increased the excitability of the cortico‐spinal system in patients with DOC following TBI (Matsumoto‐Miyazaki et al. 2016). Orexin is believed to stimulate cortical activation and regulate arousal, and acupuncture at Shuigou has been reported to promote the recovery of consciousness in TBI‐induced comatose rats via the upregulation of the expression of orexin‐1 and orexin‐1 receptor in the medial prefrontal cortex (Tan et al. 2021). Informed by traditional Chinese medical theory, ancient medical records, modern clinical practice, and relevant mechanistic studies, Shuigou has been selected as the primary acupoint in this study to facilitate the recovery of consciousness. However, it should be noted that the clinical trials included in the aforementioned meta‐analysis had several limitations. Specifically, these trials encompassed patients with both coma and prolonged DOC, utilized the Glasgow Coma Scale, which is not suitable for assessing prolonged DOC, to evaluate the severity and outcomes, and lacked sham controls. Although several studies have attempted to investigate the mechanism of acupuncture in treating DOC, the perspectives of these studies are rather singular and limited. A more in‐depth and multimodal investigation is required to evaluate the effects of acupuncture on the structure, perfusion, metabolism, electrophysiological activity, and function of critical areas in the consciousness circuitry.

Given the previous findings on the effects of EA on DOC, we initiated a randomized controlled trial called AcuDoc, dedicated to examining the efficacy of EA against DOC through behavioral and brain–computer interface (BCI) assessments and exploring its potential therapeutic mechanisms via neurophysiological and neuroimaging techniques.

## Methods

2

### Study Objectives

2.1

This study aims to explore the therapeutic effects and mechanisms of EA in patients with DOC due to TBI through a multimodal approach.

### Study Design

2.2

This is a single‐center, participant‐blinded, randomized, sham‐EA‐controlled trial. The AcuDoc trial will enroll 50 patients with DOC and 25 healthy subjects (Figure 1). Patients will be randomized to the EA group or the sham‐EA group. Each healthy subject will receive a set of neurophysiological and neuroimaging examinations but no treatments.

**FIGURE 1 brb370637-fig-0001:**
[figure not shown]
Study flow. BCI, brain–computer interface; EA, electroacupuncture; GOS‐E, Glasgow Outcome Scale‐Extended; MCS, minimally conscious state; TBI, traumatic brain injury; UWS, unresponsive wakefulness syndrome.

### Ethics

2.3

The study is performed in accordance with the principles of the Declaration of Helsinki, has been approved by the ethics committee of the Second Affiliated Hospital of Guangzhou University of Chinese Medicine (BF2023‐252‐01), and has been registered at ClinicalTrials.gov (NCT06268236, on February 12, 2024). The protocol of this trial was performed according to the SPIRIT 2013 Statement (Supporting Information). Written informed consent will be obtained from the legal representative of each participant because DOC patients are not competent to provide informed consent.

Protocol amendments will be agreed upon with the AcuDoc Study Group, Sponsor, and Funding Body before submission for ethical approval. Following ethical approval, protocol modifications will be communicated with relevant parties such as the trial investigators and the trial registry.

### Study Population

2.4

The study will include 50 adult patients with DOC due to TBI and 25 healthy subjects. Patients eligible for inclusion must meet the following criteria: (1) age ≥ 18 years; (2) with cerebral damage due to TBI; (3) diagnosed with unresponsive wakefulness syndrome (UWS) or minimally conscious state (MCS) based on at least two Coma Recovery Scale‐Revised (CRS‐R) assessments; (4) from 7 to 90 days from the onset of brain injury; (5) informed consent obtained.

Exclusion criteria are (1) with a history of neurological or psychiatric disorder before the brain injury; (2) with uncontrolled seizures or status epilepticus; (3) with unstable vital signs and requiring the use of vasoactive agents; (4) with the use of general anesthetics or central acting sedative; (5) without intact skin at acupoints or sham points; (6) with concomitant medical illness that would interfere with the outcome assessments and/or follow‐up; (7) pregnant patients; (8) currently participating in other investigational trials; (9) with high likelihood of not adhering to the study treatment or the follow‐up regimen.

Age‐ and sex‐matched healthy subjects will be included in this trial and must meet the following criteria: (1) without a history of brain injury; (2) without alcohol/substance abuse; (3) without neurological or psychiatric disorders; (4) currently not on any medication.

### Randomization

2.5

As soon as informed consent is provided, the investigator should acquire the result of randomization. Stratified randomization, employing two strata (MCS and UWS), is utilized to ensure balanced proportions of UWS and MCS patients in each group. A secure randomization software is used to perform the randomization (computerized random numbers). Patients will be randomized in a 1:1 ratio to receive EA or sham‐EA treatment.

### Masking

2.6

The EA and sham‐EA practitioners are the only investigators informed of the grouping results. Patients, their families, and all the other investigators are blinded to the allocation. To help maximize the blinding of participants, sham‐acupoints, sham‐acupuncture, and sham‐wire are used. A curtain is placed around the patient during the procedure, from the needle insertion to the determination of the maximum withstand current, to prevent other individuals from observing any physical reactions. Outcome scores are assessed independently by a qualified researcher who does not participate in the treatment and is blind to the grouping results.

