### Trial Interventions

2.7

All patients receive routine standardized neurocritical care management, including airway management, temperature regulation, blood pressure control, electrolyte balance maintenance, infection control, nutritional support, etc. Additionally, all patients undergo passive range of motion therapy and ergometer cycling therapy daily, administered by a physiatrist blinded to the group allocation.

All patients receive EA or sham‐EA treatment in the supine position at 9 am for 30 min once a day for 14 consecutive days (Figure 2). One certified acupuncturist performs EA and sham‐EA treatments for patients in both groups. Disposable sterile acupuncture needles (0.25×25 mm, Hanyi brand, Changchun AIK Medical Devices Co., China) and EA apparatuses (SDZ‐V, Hwato Brand, Suzhou Medical Appliance Factory, China) are used in both groups.

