**FIGURE 2 brb370637-fig-0002:**
[figure not shown]
Electroacupuncture and sham‐electroacupuncture treatments. EA, electroacupuncture.

Patients in the EA group receive acupuncture at Shuigou (also known as Renzhong, GV26, DU 26) and Yintang (updated number GV24+, previous number GV29). Shuigou is located on the midline above the upper lip, at the junction of the upper one‐third and lower two‐thirds of the philtrum midline (Institute of Acupuncture and Moxibustion, China Academy of Chinese Medical Sciences 2021). Yintang is located on the forehead, at the midpoint between the two medial ends of the eyebrow (Institute of Acupuncture and Moxibustion, China Academy of Chinese Medical Sciences 2021). After the skin is sterilized, sterile adhesive pads are placed in the area between the nose and upper lip and in the area between the eyebrows. Acupuncture needles are inserted through the adhesive pads approximately 10–15 mm into the skin. The acupuncture needle is inserted obliquely (30°–45°) upward to the direction of the nose for Shuigou and is inserted obliquely (15°–30°) downward to the direction of the nose for Yintang. Paired electrodes from the EA apparatus are clipped to the needle handles at Shuigou and Yintang. The EA stimulation lasts for 30 min with a wave of rarefaction and condensation (4 Hz/20 Hz) and a current intensity of the maximum withstand current within 10 mA. The maximum withstand current is defined as the maximum current intensity that does not cause any discomfort with a Nociception Coma Scale‐Revised score (Chatelle et al. 2012) above 4 and is different from the baseline value.

Patients in the sham‐EA group receive sham‐EA at sham‐Shuigou (1 cun [≈20 mm] lateral to Shuigou) and sham‐Yintang (1 cun [≈20 mm] lateral to Yintang). After the skin is sterilized, sterile adhesive pads are placed in the area between the nose and upper lip and in the area between the eyebrows. Acupuncture needles are inserted into the adhesive pads but do not pierce the skin. Paired electrodes from the EA apparatus via sham connecting cords are clipped to the needle handles at sham‐Shuigou and sham‐Yintang. The sham connecting cords are similar in appearance to the normal ones, but the inner wires in the sham connecting cords are cut off and cannot conduct electricity. The sham‐EA stimulation lasts for 30 min with a wave of rarefaction and condensation (4 Hz/20 Hz) and a current intensity of the maximum withstand current within 10 mA.

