### Neurophysiological Assessments

2.10

All patients receive two times of video‐EEG monitoring. The first EEG recording starts 20 min before the first EA or sham‐EA treatment and continues until 24 h after the treatment. The second EEG recording starts 20 min before the last EA or sham‐EA treatment and continues until 24 h after the treatment. EEG signals are collected through 19‐channel monopolar leads with Ag/AgCl cup electrodes (NicoletOne EEG System, USA), placed according to the international 10–20 system. The sampling frequency is 500 Hz and the electrode–skin impedance is lower than 5 kΩ.

All patients receive SEP and BAEP assessments before and after the 14‐day EA or sham‐EA treatment (Nicolet Monitor UltraPro S100, US). All SEPs and BAEPs are assessed for reproducibility and analyzed by one certified neurophysiologist. For SEP, monophasic rectangular‐wave 200 µs stimulus pulses are given to the median nerve, and the intensity is adjusted to produce a visible thumb twitch. A minimum of 500 stimulations are averaged per recording. For BAEP, monoaural click stimuli of 50 µs duration are delivered through shielded headphones at a frequency of 10 Hz and an intensity of 70–90 dB HL. Both ears are stimulated separately. The contralateral ear is masked by 20 dB noise. Three trials of 1,000 clicks are recorded to assess reproducibility.

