## Discussion

3

DOC is a common consequence of TBI, but the clinical management of DOC remains a great challenge despite many efforts devoted to this long‐standing problem (Thibaut et al. 2019). Many ancient records and modern studies have shown that acupuncture may have a beneficial effect on DOC due to TBI (Cavalli et al. 2018). The AcuDoc trial is the first randomized and sham‐controlled trial to investigate the therapeutic effects and mechanisms of EA in TBI‐induced DOC through a multimodal approach.

Previous randomized trials of non‐pharmacological interventions for DOC have sample sizes ranging from 10 to 30^3^ (Barra et al. 2022; Spaccavento et al. 2024; Bai et al. 2017; Angelakis et al. 2014). In this trial, we plan to enroll 50 patients, and this sample size can detect a clinically important difference of 1.3 in the total score change of CRS‐R between the two groups. Moreover, previous trials usually include DOC patients with all kinds of etiologies (Hu et al. 2024), such as stroke, hypoxic‐ischemic encephalopathy, and TBI. However, outcomes vary widely by etiology, which will bias the assessment of treatment efficacy. This trial only included patients with DOC due to TBI within 3 months and used stratified randomization to ensure balanced proportions of UWS and MCS in the two groups to minimize biases. Blinding is a challenging yet crucial procedure in conducting randomized trials of non‐pharmacological therapies for DOC (Martens et al. 2020). However, very few non‐pharmacological DOC studies have employed a sham control, and none of the previous trials investigating the effects of acupuncture or EA on DOC or coma were sham‐controlled (Chen et al. 2021; Xin et al. 2022; Matsumoto‐Miyazaki et al. 2016). Although many DOC patients are unable to perceive whether or not they are receiving acupuncture treatments, the medical care provided by physicians, nurses, or caregivers may be biased by the setting of unblinding. In this trial, we adopted a classical masking method used in previous high‐quality randomized trials of EA (Liu et al. 2017): sham acupoints, sham acupuncture, and sham conductor wire are used in the sham‐controlled group.

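### The stated curtain window ends when the current is set, so needle position and any reaction can be seen by families and bedside staff during the 30-minute stimulation on each of 14 days

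*Protocol article*

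**What the plan says.** Section 2.6 (Masking) makes the EA and sham-EA practitioners the only investigators who know the allocation: "Patients, their families, and all the other investigators are blinded to the allocation". It relies on sham points, sham needling, a sham wire and a curtain. The curtain has a stated start, end and purpose: it is in place "from the needle insertion to the determination of the maximum withstand current, to prevent other individuals from observing any physical reactions".

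Section 2.7 (Trial Interventions) describes what follows. "The EA stimulation lasts for 30 min with a wave of rarefaction and condensation", and sessions take place "at 9 am for 30 min once a day for 14 consecutive days". In the EA arm the needles are at two midline points of the face ("Shuigou is located on the midline above the upper lip"; the other point lies between the eyebrows). They go 10–15 mm in at an oblique angle and carry up to 10 mA. In the sham arm both points are about 20 mm lateral, "Acupuncture needles are inserted into the adhesive pads but do not pierce the skin", and the cord does not conduct.

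Section 2.10 adds video-EEG around the first and last sessions: "The first EEG recording starts 20 min before the first EA" or sham-EA session and runs until 24 hours after it. The second recording follows the same pattern. The Discussion explains why blinding of those around the patient matters: "the medical care provided by physicians, nurses, or caregivers may be biased by the setting of unblinding".

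**The concern.** The curtain is there to stop others seeing physical reactions, but its stated end is the moment the working current has been found. The patient is then stimulated at that current for half an hour with no stated screen. Two things that differ by arm are then open to view: where the needles stand, and whether the face responds to current.

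The sham procedure is presented in the Discussion as what sets this trial apart from earlier acupuncture and EA trials in DOC or coma, none of which was sham-controlled. If families and bedside staff can work out the arm, the co-interventions and attention that the sham is meant to equalise may differ between arms. The primary outcome is the change in a behavioural scale over those same 14 days.

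**Working it through.** The plan gives no figure on this point. The check sets the passages side by side, with one multiplication.

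1. **Unscreened time.** Inputs from section 2.7: 30 minutes of stimulation per session, 14 sessions. 30 × 14 = 420 minutes, or 420 / 60 = 7 hours per patient. This assumes that the 30 minutes start once the current is set. If current-finding falls within the 30 minutes, the figure is somewhat lower, so it is an upper bound. Needle removal is also outside the stated window.

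2. **What differs between arms in that time** (section 2.7):

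| Feature | EA | Sham-EA | Concealed by pads and look-alike cords? |
|---|---|---|---|
| Needle site | Midline, both points | About 20 mm lateral, both points | No |
| Penetration | 10–15 mm, oblique | None; needle held in the pad | Largely, by the pad |
| Current | Up to 10 mA | None; inner wire cut | The wire yes, a response to current no |

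3. **Whether reactions can persist.** The current is limited by a criterion of discomfort scoring above 4 on the Nociception Coma Scale-Revised. Smaller responses and muscle twitches are not excluded. The article does not report that they occur. It follows only that a current-driven response is possible in EA and impossible in sham.

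4. **Who is exposed.** Section 2.6 declares families and all non-practitioner investigators blinded. Section 2.7 does the same for the physiatrist who gives the daily passive-motion and cycling therapy. The Discussion names physicians, nurses and caregivers as people whose care could be affected. No section extends the curtain through stimulation or needle removal, or keeps these people away.

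5. **Whether position is informative.** An observer who knows the traditional point would recognise midline placement; the Background describes its use over more than a thousand years. Staff at a single centre who see several patients could also notice two placements. Both are inferences, not statements in the article.

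6. **Video-EEG.** Each recording runs from 20 minutes before a session to 24 hours after it, so the session lies inside the file. The time points for immediate effects in section 2.13 are 10 minutes before treatment and 10 minutes, 60 minutes, 6 hours and 24 hours after. None falls within the session, so the treatment segment can be withheld without losing a planned time point.

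**The case against.** The strongest reply is that this is a condensed article. Rules on bedside access and the handling of EEG files usually sit in the full protocol, so their absence proves nothing. That stands for those rules. It does not answer the curtain, because the article itself fixes the window at both ends.

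A second reply is that the riskiest phase for visible reactions, insertion and the search for the limit, is screened, and that the current used afterwards is capped. This reduces the chance of a visible reaction but leaves needle position in view. Figure 2, which depicts the treatments, is not available here, so how clearly position shows with the pads in place cannot be fully judged.

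Several stronger readings are tempting but unsupported:

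- **That the CRS-R assessor is unblinded.** Sections 2.6 and 2.9 declare the assessor blind, and section 2.6 says the assessor takes no part in treatment. The daily CRS-R comes after the session, and nothing places the assessor at the bedside during it. Exposure is a possibility only.
- **That EEG readers are unblinded.** The planned time points exclude the session, and nothing says that analysts view that segment or its video. The file merely contains material that could reveal the arm to someone who opens it.
- **That skin marks reveal the arm.** No section describes marks. The needles are 0.25 mm wide and pass through pads.
- **That the protocol concedes bias in the primary outcome.** The Discussion says care may be biased, not the rating.

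**Conclusion.** The point holds for the curtain window and for families and bedside staff. As written, the screen misses its own stated purpose for up to 7 hours per patient, during which needle site, and possibly reactions, distinguish the arms. These observers can learn the allocation; the article does not show that they will.

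The resulting bias in the CRS-R change cannot be derived from the document. Any figure in points, or any inflated false-positive rate, would rest wholly on an invented shift, so none is given. The conclusion assumes that the curtain is used as described at every session and that no unshown document extends it. It is a weakness worth correcting because the remedy is simple, not a defect that invalidates the design.

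**What to change.** **Section 2.6.** State that in both arms the curtain stays closed from needle insertion until needles, pads and leads have been removed, and that outcome assessors stay away from the bedside during sessions.

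**Section 2.10.** State that the treatment segment of each video-EEG, with its video, is withheld from those who analyse the EEG. Someone who already knows the allocation can do this. The segment should end before the 10-minute post-treatment time point.

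**Cost.** A few sentences of text, a short step for each EEG file, and a restricted direct view of the patient for about 30 minutes a day. The site would need to settle how observation continues behind the curtain. Randomisation, sample size, outcomes and analysis time points are unchanged.

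Opaque patches over the needle sites during the CRS-R are not advised. They would cover parts of the face while visual, verbal and arousal responses are being scored, and could disturb the primary measure.
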